## Abstract

**Introduction::**

Diastolic heart failure (DHF) is an important pathological type of heart failure, that involves multiple organ dysfunction and multiple complications. The prevalence of DHF is high, and effective treatments are lacking. Chinese herbs are an alternative therapy for DHF. Shen’ge formula (SGF) is a classical formula from which patients can benefit, but convincing evidence of its efficacy is lacking. Therefore, we designed this randomized controlled trial protocol.

**Methods/design::**

This randomized, double-blind, placebo-controlled clinical trial will evaluate the efficacy and safety of SGF in the treatment of DHF. A total of 130 patients with DHF will be enrolled in the trial and treated with SGF granules or placebo for 12 weeks and followed up for 12 weeks. The primary outcome measurement will be to changes in plasma N-terminal brain natriuretic peptide precursor before versus after treatment, while the second primary outcome measurement will be changes in heart function before versus after treatment and the 12-week follow-up period. It will also include echocardiography, a cardiopulmonary exercise test, cardiac function grading, traditional Chinese medicine syndrome score, and the Minnesota Heart Failure Quality of Life Scale. Adverse events will be evaluated throughout the trial.

**Discussion::**

The results of this trial will demonstrate whether SGF could alleviate symptoms, improve cardiac function, reduce readmission rates, and improve quality of life of patients with DHF.

**Trial registration::**

Chinese Clinical Trial Register, ChiCTR2000036533, registered on August 24, 2020.

## Introduction

1

Diastolic heart failure (DHF) is also known as heart failure (HF) with preserved ejection fraction (HFpEF). The prevalence of DHF has been increasing at a rate of 1% per year, increasing from 38% to 54% over the past 20 years.^[1]^ The data collected from the American College of Cardiology's National Cardiovascular Data Registry Practice Innovation and Clinical Excellence showed that 56.5% (n = 622 866) of 1 103 386 patients had HFpEF.^[2]^ A study also showed that more than 90% of patients had HF with diastolic dysfunction independent of ejection fraction.^[3]^ However, as a current major public health problem, there is no effective treatment for DHF,^[4]^ and the interventions mainly include smoking cessation, moderate exercise, weight control, and the treatment of basic diseases.^[5]^ Moreover, DHF will be a major cause of HF in the next 10 years and involves multiple organ dysfunction with multiple complications.^[6]^

Traditional Chinese medicine (TCM), a verified complementary or alternative treatment for patients with HF,^[7–11]^ has been used to treat various heart diseases in China for thousands of years. In our study, Shen’ge formula (SGF), a representative TCM formula, consisting of ginseng and gecko (Table 1) in a 3:1 proportion by weight will be used as a therapeutic drug to treat patients with DHF. A previous study showed that SGF could improve cardiac function and myocardial contractility in HF patients.^[12]^ Gu Ben Pei Yuan San, another TCM formula containing ginseng, gecko, and other herbs, was suggested to improve cardiac function and repair the myocardium in adult mice after apical resection or myocardial infarction.^[13]^ To promote the use of SGF for the treatment of DHF worldwide, randomized, double-blind, placebo-controlled clinical trials are still needed to prove its effectiveness. All of the information for this study was obtained from the Chinese Clinical Trial Registry (registration number: ChiCTR2000036533; http://www.chictr.org.cn).

**Table 1 T1:** Components of SGF.

Latin scientific name	English name	Chinese name
*Panax ginseng C.A.Mey.*	Ginseng	Renshen
*Gekko gecko Linnaeus*	Gecko	Gejie

SGF = Shen’ge formula.

This randomized double-blind placebo-controlled clinical trial of DHF will include 12 weeks of clinical intervention and 12 weeks of follow-up. Changes in plasma N-terminal brain natriuretic peptide precursor (NT-proBNP) before versus after treatment will be the primary outcome measure. Changes in cardiac ultrasound, cardiopulmonary exercise test, cardiac function grade, TCM syndrome score and Minnesota Heart Failure Quality of Life Scale will be the secondary outcome measure. We will also assess its safety aspects by thoroughly documenting any adverse events (AEs) that occur.

## Methods

2

### Study design

2.1

This randomized double-blind placebo-controlled clinical trial will investigate the efficacy and safety of SGF in DHF patients. We will recruit 130 patients with DHF from LongHua Hospital affiliated with the Shanghai University of TCM. A total of 130 participants will be equally randomized into the SGF or placebo group. Patients in the SGF group will take 4 g SGF per day for 12 weeks, while patients in the placebo group will take SGF placebo for the same duration. The trial process is summarized in Figure 1.

**Figure 1 F1:**
[figure not shown]
Study flowchart. The entire trial will last 24 weeks including 12 weeks for oral drugs and another 12 weeks for follow-up. DHF = diastolic heart failure, SGF = Shen’ge formula.

### Ethical issues

2.2

The clinical trial will follow the Declaration of Helsinki and the Ethical Guidelines for Clinical Research. The trial protocol was approved by the Institutional Review Board of Longhua Hospital affiliated with Shanghai University of Traditional Chinese Medicine (approval number: 2020LHSB053). Additionally, the protocol has been registered in the Chinese Clinical Trial Registry (ChiCTR2000036533). Personal information about potential and registered participants will be collected for use only in this trial, and we will not share or retain such personal information when it is not necessary.

### Study participants

2.3

Participants will be recruited from LongHua Hospital affiliated with Shanghai University of Traditional Chinese Medicine. Recruitment posters and social application advertisements will be distributed. The objective, approaches, and potential side effects and advantages of this study will be fully explained in writing to the patient and his or her family or designated representative. Before entering the trial, patients and their families must provide written informed consent, and patients and their families have the right to withdraw from the study at any time. Informed consent will be retained as clinical trial documents for future reference. The planned enrollment period is 24 months.

### Main inclusion criteria

2.4

(1)Patients who meet the diagnostic criteria of Western medicine and TCM;(2)Patients with New York Heart Association (NYHA) grade II–IV cardiac function;(3)Patients aged 18 to 80 years;(4)Patients who are not taking forbidden medicine and are able to complete the trial; and(5)Patients who participate in this clinical trial voluntarily, understand its objectives, and provide written informed consent.

### Main exclusion criteria

2.5

1.Shock, acute myocardial infarction, pulmonary embolism, infectious endocarditis, severe hepatic, or renal insufficiency;2.Currently pregnant or lactating or current mental disorder;3.Seriously ill patients with a life expectancy of less than 6 months; or4.Patients who are taking other TCM and unwilling to stop.

### Randomization and allocation

2.6

Using the random number method in Excel software, the random arrangement of treatment (therapeutic versus control drug) received by 130 subjects will be generated by the given seed number of 2020, and the corresponding treatment allocation for the serial number of 1 to 130 will be listed. According to the order in which the subjects are enrolled, the researchers will fill in a random number on the medical record sheet and distribute the experimental drugs matching the random number.

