##### NYHA cardiac function classification

2.9.2.3

NYHA cardiac function classification: Cardiac function I, patients with heart disease but unrestricted activity in whom normal physical activity does not cause fatigue, palpitations, shortness of breath, or angina. Cardiac function II, heart function and physical activity are limited by mild heart attack, no discomfort when resting but normal activity can lead to fatigue, heart palpitations, shortness of breath, or angina. Cardiac function III, heart disease, limited physical activity, less than the usual general activity causes symptoms. Cardiac function IV, heart patients cannot perform any physical activity, and in the resting state can experience symptoms of HF or angina pectoris plus aggravating discomfort after physical activity.

Significant effect: Cardiac function was restored to level I or improved by 2 levels.

Effective: Cardiac function improves by 1 but not 2 levels.

No effect: No change in cardiac function; deterioration; cardiac function decreased by 1 or more levels.

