### Statistical analysis

2.16

The statistical analysis will be performed using SPSS 20.0. If the measurement data are normally distributed with homogeneous variance, the mean ± standard (± s) will be used for the statistical analysis and the t-test will be used for the intergroup comparisons. If the data do not follow a normal distribution, the rank sum test will be used to make statistical inferences. Enumeration data will be statistically described as frequency, constituent ratio, and rate. Comparison of indicators with dichotomous or multi-classification disorders will be performed using the *χ*^2^ test. The rank sum test will be used to compare groups of ordered classification analysis indicators. Statistical significance will be set at *P* < .05.

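### The NYHA response grade depends on entry class, but the planned rank sum test does not stratify by class; a stratified test would gain roughly 1 to 8 points of power on this secondary outcome

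*Protocol article*

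**What the plan says.** Four parts of the protocol article bear on this.

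- **Main inclusion criteria (2.4):** "Patients with New York Heart Association (NYHA) grade II–IV cardiac function". The expected mix of classes is not stated.
- **NYHA cardiac function classification (2.9.2.3):** the top grade is defined as "Significant effect: Cardiac function was restored to level I or improved by 2 levels", the middle grade as "Effective: Cardiac function improves by 1 but not 2 levels". Everything else is no effect.
- **Statistical analysis (2.16):** "The rank sum test will be used to compare groups of ordered classification analysis indicators". No stratum or baseline term is mentioned, here or for continuous outcomes, where "the t-test will be used for the intergroup comparisons".
- **Randomization and allocation (2.6):** one random sequence is generated and "the corresponding treatment allocation for the serial number of 1 to 130 will be listed". It is used in sequence: "According to the order in which the subjects are enrolled, the researchers will fill in a random number on the medical record sheet". No stratification factor is named.

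**The concern.** The grading rule makes entry class prognostic for the grade, even if patients of every class are equally likely to improve. A one-step gain is a *Significant effect* for someone who enters in class II, and only *Effective* for someone who enters in class III or IV.

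A rank sum test that pools all classes ranks these patients against each other. Differences that come only from entry class then count as noise, and a chance surplus of class II patients in one arm is not adjusted for. At stake is power on one secondary outcome, and how easily its result can be read if the arms happen to differ at entry.

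**Working it through.** **1. The plan's own figures.** The document states no power for the NYHA grade. Its only size calculation is for NT-proBNP: ((1.645 + 1.282)/(12/30))² + ½ × 1.645² = 53.55 + 1.35 = 54.9, against 54 stated; 54 × 1.2 = 64.8, hence 65 per group. Only the arm size of 65 is used below.

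**2. Grade by entry class, from 2.9.2.3.**

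| Entry class | One step up | Two steps up |
|---|---|---|
| II | I: Significant | not possible |
| III | II: Effective | I: Significant |
| IV | III: Effective | II: Significant |

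A move from II to I also fits the literal wording of the middle grade. It is graded Significant here because level I is reached. Suppose 30% improve in every class, and one in ten class III-IV improvers gains two levels. The split none/Effective/Significant is then 70/0/30% in class II and 70/27/3% in class III-IV: equal improvement, different grades.

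**3. Chance imbalance.** With K of 130 patients in class III-IV and 65 per arm, the number X in one arm is hypergeometric: P(X = x) = C(K, x) C(130 − K, 65 − x) / C(130, 65). The difference in share is |2x − K|/65. K is assumed.

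| K (share) | P(at least 10 points) | P(at least 15 points) |
|---|---|---|
| 39 (30%) | 0.25 | 0.055 |
| 52 (40%) | 0.21 | 0.107 |
| 65 (50%) | 0.29 | 0.079 |

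The columns are not monotone because differences come in steps of 2/65. For K = 52 the first difference above 10 points is 8/65 = 12.3; for K = 39 or 65 it is 7/65 = 10.8.

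**4. Power.** The van Elteren statistic is Z = Σ wₛ(Tₛ − Eₛ) / √(Σ wₛ²Vₛ). In stratum s of size Mₛ, Tₛ is the rank sum of the SGF arm, Eₛ its null mean, Vₛ its tie-corrected variance, and wₛ = 1/(Mₛ + 1). Simulation used 20,000 trials per cell, 65 per arm, two-sided 0.05, and classes II, III and IV as strata. Four assumed mixes of II/III/IV (50/40/10, 30/50/20, 70/27/3, 34/33/33) were crossed with four assumed patterns of improvement, placebo to SGF:

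- A: 30 to 55% in every class.
- B: class II improves less (15 to 35%; III-IV 40 to 65%).
- C: class II improves more (45 to 68%; III-IV 22 to 40%).
- D: class IV rarely improves (II 30 to 55%, III 35 to 58%, IV 15 to 30%).

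| Pattern | Planned (50/40/10) | Stratified test only | Stratified test and list | Gain from test alone, all mixes (points) |
|---|---|---|---|---|
| A | 0.814 | 0.826 | 0.829 | 1.0 to 1.2 |
| B | 0.775 | 0.779 | 0.792 | 0.4 to 0.7 |
| C | 0.608 | 0.690 | 0.688 | 6.1 to 8.2 |
| D | 0.774 | 0.785 | 0.788 | 0.9 to 2.8 |

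The test gains in all 16 scenarios. Stratifying the list as well changes power by −0.4 to +1.5 points; the simulation standard error of such a difference is about √(2 × 0.8 × 0.2/20,000) = 0.4 points. With the planned test kept, a stratified list gives 0.813 against 0.814 in pattern A at 50/40/10. Merging III with IV leaves the gain from the test in the same rough range. A further run at an odds ratio of 2.3 gave about 2 to 8 points at 65 or 54 per arm.

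**5. Type I error (50/40/10, null patterns A and C).** Single list with planned test: 0.052 in both. Single list with stratified test: 0.052 and 0.051. Stratified list with stratified test: 0.048 and 0.050. Stratified list with planned test: 0.048 and 0.038, so conservative in the second.

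**The case against.** **Nothing stated is invalid.** A single list in a one-centre trial of 130 is legitimate, and the planned test holds its level. This stands. A reader might infer false positives, because the planned test's type I error is 5.4 to 8.8% in simulated allocations at least 15 points out of balance. That figure is conditional on 5 to 11% of allocations; the unconditional error already averages over them and is about 5%.

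**A reader might also blame the allocation list.** The numbers do not support that. Once the test is stratified, the list adds little or nothing; with the planned test it adds nothing reliable. Nor can the silence on blocks in 2.6 be taken as a fault: a condensed article may leave block details out, and the cost would be small. A 45:35 split after 80 patients still keeps 4 × 45 × 35/80² = 98.4% of the information.

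**Strata may belong in an analysis plan that is not shown.** This is the best argument against raising the point. But 2.16 does name the test for ordered outcomes, and as named it is the plain one. If an analysis plan already stratifies it by entry class, the point is met.

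**Only a secondary outcome is quantified, on assumed rates.** This stands, and it limits the point to an inexpensive improvement.

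**Conclusion.** The point holds as a minor gain in efficiency, not as an error or a bias. The planned rank sum test is valid for the NYHA response grade but ignores an entry characteristic built into the grade. Stratifying the test by entry class gains roughly 1 to 8 points of power: under 1 point where class II improves less, 1 to 3 in most other scenarios, and 6 to 8 only where class II improves more.

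The size rests on assumed class mixes, response rates and two-level gains, and on grading II to I as Significant. The document gives none of the rates.

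The result does not carry over to the primary outcome. For NT-proBNP (two-sample comparison, difference 12, SD 30, 54 per arm, two-sided 0.05), power would go from 0.547 to 0.568 if class explained 5% of the variance of the change and to 0.591 at 10%. It would not move if class explained almost none. The document gives no such figure.

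**What to change.** **In 2.16**, prespecify that the NYHA response grade is compared between arms with a van Elteren test, a rank sum test stratified by entry NYHA class (II v III-IV). Two strata avoid a sparse class IV stratum. **In 2.9.2.3**, say which grade a move from II to I receives, since it fits two definitions.

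**Optional, in 2.6:** separate 1:1 lists for the same two strata, as an aid to baseline balance. Do this only together with the stratified test, because the planned test would then be slightly conservative.

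**Cost:** one sentence in 2.16 and a clarification in 2.9.2.3, with no extra patients or visits; entry class is already assessed for eligibility. If SPSS 20.0 as installed does not offer the test, it can be computed from the within-stratum rank sums. If recruitment has begun, the test can still be fixed before unblinding. One small downside is that NYHA class is graded by a clinician, and misgraded entry class weakens the gain.

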### Blinding

2.7

TCM granules (SGF) and placebo will be packaged identically. The label on each package includes the drug number, quantity, method of administration, storage conditions, the label “for clinical research only,” and the drug supply unit. The 2 drugs will be randomly cataloged, and the doctors in charge of the general manager plan will issue medical advice for drug distribution, the nurses will issue the drugs, and the doctors in charge of the patients will register the drug distribution. The doctors and nurses in charge of the patients will be blinded to the patients’ drug allocations.

### Interventions

2.8

#### TCM intervention

2.8.1

In the SGF group, patients will be instructed to dissolve SGF (4 g) in 50 mL of hot water and take the solution orally once a day for 12 weeks, while patients in the placebo group will take SGF placebo in the same way. The SGF and SGF placebo will be manufactured, packaged, and labeled by the Department of Pharmacy, Longhua Hospital Affiliated to Shanghai University of Chinese Medicine. SGF consists of ginseng (Renshen, 3 g) and gecko (Gejie 1 g). All herbs will be crushed into a powder using a pulverizer and collected after being subjected to No. 10 sifter-mediated selection. Finally, the SGF will be packed in individual bags (4 g each). For the control group, SGF placebo will also be prepared by the above department to achieve a similar color, smell, taste, and texture as the SGF. The research drugs will be stored in cool and dark places, placed in dry places away from light, managed and distributed by special personnel, and tracked carefully.

#### Conventional Western medicine intervention

2.8.2

All enrolled patients will be administered basic drug therapy according to the Chinese Guidelines for the Diagnosis and Treatment of Heart Failure, Chinese Society of Cardiology (2018). Angiotensin-converting enzyme inhibitors or angiotensin receptor blockers, β-receptor blockers, diuretics, digitalis drugs, and nitrate drugs will be selected for specific situations.

#### Forbidden treatments and drugs

2.8.3

(1)Any other TCM methods are not allowed (herbs except for SGF or SGF placebo, acupuncture, cupping, etc).(2)Medications outside of the guidelines are not allowed.(3)The dosage, duration, and name of any intervention must be recorded thoroughly in the case report form.

### Outcomes

2.9

#### Primary outcomes

2.9.1

NT-proBNP levels will be determined using an enzyme-linked immunosorbent assay kit before and after drug administration (week 0 and week 12).

#### Secondary outcomes

2.9.2

##### Echocardiography

2.9.2.1

Echocardiography includes left ventricular mass index, E/E′ ratio, pulmonary systolic pressure, and right ventricular end-diastolic volume.

##### Cardiopulmonary exercise test

2.9.2.2

Peak oxygen uptake, anaerobic threshold, and other indicators will be detected at weeks 0 and 12.

##### NYHA cardiac function classification

2.9.2.3

NYHA cardiac function classification: Cardiac function I, patients with heart disease but unrestricted activity in whom normal physical activity does not cause fatigue, palpitations, shortness of breath, or angina. Cardiac function II, heart function and physical activity are limited by mild heart attack, no discomfort when resting but normal activity can lead to fatigue, heart palpitations, shortness of breath, or angina. Cardiac function III, heart disease, limited physical activity, less than the usual general activity causes symptoms. Cardiac function IV, heart patients cannot perform any physical activity, and in the resting state can experience symptoms of HF or angina pectoris plus aggravating discomfort after physical activity.

Significant effect: Cardiac function was restored to level I or improved by 2 levels.

Effective: Cardiac function improves by 1 but not 2 levels.

No effect: No change in cardiac function; deterioration; cardiac function decreased by 1 or more levels.

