### TCM syndrome score

2.10

This score form is constitutive of 2 parts: symptoms and signs. There are a total of nine appraisable items including palpitation, shortness of breath, lassitude, asthma, felling cold, chest distress, edema, oliguria, and abdominal distention. Each item consists of 4 levels. The minimum score is 0, and the maximum score is 54. Higher scores indicate more severe conditions. The scores and details of TCM syndromes are presented in Table 2. The scores are determined using the semi-quantitative integral method (0–6 points) according to the severity of clinical symptoms.

**Table 2 T2:** Traditional Chinese medicine syndrome score.

Syndromes	None	Mild	Moderate	Severe
Palpitation	None	Slight palpitations during activities; able to work	Obvious palpitations during activities; relief after rest	Unable to join routine activities
Shortness of breath	No syndrome	Short of breath after slight activity	Short of breath after moderate activity	Short of breath during rest
Fatigued	None	Slight fatigue; able to work	Heavy and barely able to work or complete routine activities	Too heavy to work or complete routine activities
Asthma	None	Slight wheezing; able to work	Frequent wheezing; able to sleep	Unable to lie down and sleep
Felling cold	None	Fear cold	Need to add clothes	Still feel cold after adding clothes
Chest distress	None	Slight	Often	Always
Edema	None	Slight edema morning and night	Pitting edema (+to++)	Pitting edema (>++)
Oliguria	None	Little urine (>1000 mL within 24 h)	Little urine (<400 mL within 24 h)	Little urine (<100 mL within 24 h)
Abdominal distention	None	Slight	Obvious	Like bulge and cannot press

Scores: Mild = 2, Moderate = 4, None = 0, Severe = 6.

Significant effect: Clinical primary and secondary symptoms disappeared partially or completely, syndrome score decreased by > 70%. Effectiveness: Clinical symptoms improved significantly, syndrome scores decreased by 30% to 70%. Null: Treatment syndrome score decreased by < 30%. Aggravation: Post-treatment points exceed pre-treatment points.

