### Safety assessments

2.12

AE time, severity, duration, action taken, and outcomes will be recorded truthfully on the designated case report forms (CRFs) during the study. Mild, moderate, and severe labels will be used to describe the intensity of each AE and assess possible associations between each AE and the study or control drug. If a severe AE occurs during the trial, the patients will be suspended from the trial and treated as a lost case. For the safety assessment, the patients’ blood, urine, and kidney and liver function will be tested before and after treatment. To protect privacy, all participants will be visited in a closed room and given the option to withdraw at any time.

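### The NYHA response grades are not mutually exclusive for a class II patient who reaches class I, and the bottom grade pools worsening with no change

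*Protocol article*

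**What the plan says.** Main inclusion criteria (2.4) admit "Patients with New York Heart Association (NYHA) grade II–IV cardiac function", so baseline class can be II, III or IV.

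Section 2.9.2.3 then defines three response grades:

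- Top: "Significant effect: Cardiac function was restored to level I or improved by 2 levels".
- Middle: "Effective: Cardiac function improves by 1 but not 2 levels".
- Bottom: "No effect: No change in cardiac function; deterioration; cardiac function decreased by 1 or more levels".

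Nothing says which grade applies when a patient meets two definitions.

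The next outcome, the TCM syndrome score (2.10), is graded differently. It has a null grade and, separately, "Aggravation: Post-treatment points exceed pre-treatment points".

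Statistical analysis (2.16) gives a general rule for ordered categories: "The rank sum test will be used to compare groups of ordered classification analysis indicators". It does not name NYHA class or the NYHA response grades.

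**The concern.** A response scale should place each patient in exactly one grade. Here the top grade is defined partly by the class reached and partly by the number of levels gained, while the middle grade is defined only by levels gained. The two criteria collide where a one-level gain also reaches class I, which happens only from class II.

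The bottom grade raises a separate issue. A patient who goes from II to III and a patient who stays at II receive the same grade. A treatment that worsens some patients would therefore score the same on this scale as one that leaves them unchanged. The protocol draws that distinction for the TCM score but not for NYHA.

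At stake is the interpretability of one secondary outcome. If the graded form is what gets compared between arms, its result depends on a coding choice the document does not fix, and it carries no information about deterioration.

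**Working it through.** The plan states no figure to reproduce, so the check is an enumeration of the definitions followed by two illustrations.

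**Step 1: all transitions.** Three eligible baseline classes (2.4) times four possible later classes gives 3 × 4 = 12. Applying the definitions in 2.9.2.3 literally:

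| Baseline | to I | to II | to III | to IV |
|---|---|---|---|---|
| II | significant **and** effective | no effect | no effect (worse) | no effect (worse) |
| III | significant | effective | no effect | no effect (worse) |
| IV | significant | significant | effective | no effect |

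Eleven transitions map to one grade. One, II to I, maps to two. Class I is the only class better than II, so that one cell contains every class II patient who improves. Three transitions are worsening (II to III, II to IV, III to IV), and all three share a grade with the three unchanged cells.

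**Step 2: what each tie-break implies.** If II to I is graded *significant*, a one-level gain earns the top grade from class II but only the middle grade from III or IV, so the grade depends on baseline class. If II to I is graded *effective*, no class II patient can reach the top grade.

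**Step 3: does the tie-break move a test?** The counts are assumed, 65 per arm: 20 vs 10 patients moving II to I, 5 vs 5 other *significant*, 10 vs 10 other *effective*, the rest *no effect*.

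- II to I as *significant*: grades 25/10/30 vs 15/10/40, rank sum p = 0.053.
- II to I as *effective*: grades 5/30/30 vs 5/20/40, rank sum p = 0.116.

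The p-value roughly doubles (0.116 / 0.053 ≈ 2.2), but both values are above 0.05.

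**Step 4: what pooling loses.** The counts are assumed, 65 per arm, with 10 *significant* and 20 *effective* in each arm.

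- One arm has 20 unchanged and 15 worse; the other has 33 unchanged and 2 worse.
- Pooled bottom grade: 20 + 15 = 35 and 33 + 2 = 35. The arms are identical, rank sum p = 1.0.
- Separate worse grade, four-grade rank sum: p = 0.26.
- Worse vs not worse, 15/65 vs 2/65: Fisher exact p ≈ 0.001.

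So the three-grade scale removes the imbalance completely. Adding a fourth rank to the same test recovers little of it here; showing the worsened counts by arm is what makes it visible.

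**The case against.** The strongest reply is that the text nearly resolves its own overlap. A gain from III to I or from IV to II already counts as two levels, so the clause about reaching class I adds something only for II to I and for the three-level gain IV to I. If II to I were merely *effective*, that clause would do very little. Reading from best grade to worst, II to I is *significant*. This stands as the most natural reading. It is still not stated, the middle definition literally includes II to I, and adopting it brings the dependence on baseline class shown above.

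Several stronger readings are tempting and are not supported:

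- *Many patients per arm are ambiguously graded.* Only class II patients who improve are affected. Any head count would need a class II share and an improvement rate, and the document gives neither.
- *Assessors will disagree.* The grade follows arithmetically from two recorded NYHA classes, so a single derivation rule can settle it for everyone. Treating doctors and nurses are blinded (2.7), so no bias between arms is apparent.
- *The trial hides harm.* The raw classes must be recorded to derive the grades and can be tabulated. Section 2.12 also states that "AE time, severity, duration, action taken, and outcomes will be recorded truthfully", and the TCM score has its own worsening grade. The loss is confined to this graded outcome.
- *The rank sum test will be applied to these grades.* Section 2.16 speaks of ordered indicators in general. NYHA class I–IV is itself ordered and could be the tested form.
- *The tie-break changes the conclusion.* In the illustration it moves the p-value without crossing 0.05.

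It is also fair to say that dependence on baseline class does not bias a randomised comparison in expectation, and that ordinal regression is a preference, not the correction of an error.

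**Conclusion.** The point holds in a limited form. As written, the NYHA response grades overlap at one of 12 transitions, II to I, which is the only improvement available to an eligible class II patient. The bottom grade also pools worsening with no change, so the graded outcome cannot show a difference between arms in NYHA deterioration. Both follow from definitions the article states, not from detail it leaves to another document.

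The number of patients affected cannot be derived. The p-values above rest on assumed counts and show only how the rules behave; they are not forecasts for this trial. The outcome is secondary, and the primary NT-proBNP analysis and the sample size do not depend on it. This is a modest correction, worth making because it is cheap and because the derivation rule is best fixed before the data are unblinded.

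**What to change.** In 2.9.2.3:

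1. Make the grades exclusive, for example by defining *effective* as an improvement of one level without reaching class I. This adopts the most natural reading and states it.
2. Split the bottom grade into *no change* and *worse*, and report the count in each of the four categories by arm, as the TCM score already allows.

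In 2.16, preferably add one line: compare end-of-treatment (week 12) NYHA class, I to IV, between arms by ordinal (proportional odds) regression adjusted for baseline class, and keep the response grades as description. This avoids the tie-break, uses worsening as well as improvement, and accounts for baseline class directly.

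The cost is a few lines of wording. No new data are needed. The small downside is less direct comparability with trials that use the three-grade scale; the three grades can still be shown by adding *no change* and *worse* together.
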